## Abstract

**Background:**

People with dementia progressively lose cognitive and functional abilities. Interventions promoting exercise and activity may slow decline. We developed a novel intervention to promote activity and independence and prevent falls in people with mild cognitive impairment (MCI) or early dementia. We successfully undertook a feasibility randomised controlled trial (RCT) to refine the intervention and research delivery. We are now delivering a multi-centred RCT to evaluate its clinical and cost-effectiveness.

**Methods:**

We will recruit 368 people with MCI or early dementia (Montreal Cognitive Assessment score 13–25) and a family member or carer from memory assessment clinics, other community health or social care venues or an online register (the National Institute for Health Research Join Dementia Research). Participants will be randomised to an individually tailored activity and exercise programme delivered using motivational theory to promote adherence and continued engagement, with up to 50 supervised sessions over one year, or a brief falls prevention assessment (control). The intervention will be delivered in participants’ homes by trained physiotherapists, occupational therapists and therapy assistants. We will measure disabilities in activities of daily living, physical activity, balance, cognition, mood, quality of life, falls, carer strain and healthcare and social care use. We will use a mixed methods approach to conduct a process evaluation to assess staff training and delivery of the intervention, and to identify individual- and context-level mechanisms affecting intervention engagement and activity maintenance. We will undertake a health economic evaluation to determine if the intervention is cost-effective.

**Discussion:**

We describe the protocol for a multi-centre RCT that will evaluate the clinical and cost-effectiveness of a therapy programme designed to promote activity and independence amongst people living with dementia.

**Trial registration:**

ISRCTN, ISRCTN15320670. Registered on 4 September 2018.

## Background

People living with dementia experience progressive and irreversible loss of memory and other cognitive functions, which is severe enough to affect daily functioning [1–3]. Loss of ability occurs due to multiple factors, including cognitive impairment (memory loss, apraxia, executive dysfunction), dementia-related motor and balance impairment, physical co-morbidity, deconditioning and loss of opportunity [2–4]. Restricted opportunity is often due to concerns about safety, including risk of falling, and failure to adapt activities to residual or individual abilities [5, 6]. Mild cognitive impairment (MCI) comprises cognitive impairments that do not interfere with everyday activities, but which progress to dementia at the rate of about 10% per year [7, 8].

Moderate or vigorous intensity exercise, two to three times a week, improves strength, gait speed and performance in activities of daily living (ADLs) [9–13] and may slow cognitive decline [9, 12, 14–19]. Strength, balance and dual-task training can improve executive function, dual-task performance and gait parameters [20–25]. Functionally oriented therapy can improve ability in ADLs [15, 26–28]. Progressive strength and balance training in older people, with and without dementia, reduces risk of falling and reduces carer strain and it can also potentially benefit quality of life, mood and confidence [8–13, 29, 30].

FINALEX, a 12-month trial of an intensive, home-based, supervised exercise programme for people with dementia demonstrated a reduction in decline of ADLs and halved the rate of falling [31]. This study showed that, with the right support, people with dementia can achieve and sustain an intensity of exercise needed to gain health benefits. The challenge is how to achieve sufficient participation, adherence and persistence in routine health and social care services. Additionally it is necessary to establish how to translate individually tailored home-based programmes for people with dementia into sustainable programmes that are deliverable in the community.

A clinical academic team comprising academic researchers, occupational therapists, physiotherapists, rehabilitation support workers, health psychologists, nurses, geriatricians and Patient and Public Involvement (PPI) collaborators developed a complex intervention aimed at promoting activity and independence and reducing risk of falls for people living with MCI or mild dementia (the PrAISED intervention) [32]. The core principles of the intervention include 150 min of physical activity per week (including balance-challenging exercises), activities which are both active and functional, encouraging positive risk taking, facilitating community or environmental access and promoting independence [32]. The aim in intervening early is to enable people to ‘live well’ with dementia, prevent crises and establish positive health habits before the inevitable progression of dementia.

The feasibility and practicability of delivering and evaluating the intervention has been established in a prior study with 60 participants [33] (Goldberg et al., Promoting Activity, Independence and Stability in Early Dementia (PrAISED): a feasbility, multisite, randomised controlled trial, forthcoming). The feasibility randomised controlled trial (RCT) enabled refinement of mechanisms for tailoring the therapy programme to individuals’ needs and characteristics. Research procedures were updated for the present RCT to replace or omit measurement scales that did not perform satisfactorily, and to ensure that an informant was recruited for each participant. Additionally, we established that blinded ascertainment of outcome data was impossible, as inadvertent revelation of group allocation by participants occurred in more than 80% of cases, despite considerable efforts to maintain blinding [34].

Informed by results from the feasibility study, we now present a protocol for a definitive, multi-centred RCT (protocol version 2.3, 4th April 2019). The protocol has been extensively peer reviewed as part of the funding application process.

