### Randomisation

Participants will be individually randomised, stratified by site, the presence of a co-resident carer and history of previous falls, using a dynamic, adaptive allocation algorithm [36] accessed by a secure web portal to the system held at the North Wales Organisation for Randomised Trials in Health Clinical Trials Unit (NWORTH CTU), Bangor University. The randomisation system will be maintained by a statistician independent of the analysis and research teams. Access to the study website will be password protected. After randomisation and irrespective of intervention group allocation, a member of the local research team will inform the participant about the treatment and follow-up plan and inform the therapy provider so a visit can be arranged.

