### Sample size and justification

The primary outcome is the Disability Assessment for Dementia (DAD) at 12 months [37]. A sample size of 184 participants per group, including 23% attrition (based on previous studies [10, 31]), has 80% power to detect changes in the disability outcome, DAD, with effect size 0.5 (11 points on a baseline of 70, standard deviation 22, data from [10, 13]). This sample size has been rechecked using data from the feasibility study and confirmed to be a conservative estimate.

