### Assessment of efficacy

Analyses will be conducted on an intention-to-treat basis. Missing data for outcome measures will be imputed, using multiple imputation, if more than 5% of the data are missing and data are shown to be missing at random.

We will compare the DAD scores between the intervention and the control groups, adjusting for stratifying variables and any baseline imbalances in an ANCOVA model. Adjusted mean differences between groups and standardised effect size estimates (equivalent to Cohen’s *d* [59]) will be calculated.

Rate of falls will be compared between the intervention and the control groups using the incidence rate ratio, from a negative binomial regression model, adjusted for baseline imbalance or variables with prognostic importance [60, 61].

Other secondary outcomes will be compared between the intervention and the control groups using ANCOVA to adjust for baseline imbalance or variables with prognostic importance.

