## Discussion

We developed a complex intervention, and successfully conducted a feasibility RCT to demonstrate the practicability of its delivery, and of undertaking research procedures in this population and setting [32, 33]. We now present the protocol for a multi-centre RCT to determine its clinical and cost-effectiveness.

Dementia is progressive, affecting memory, other cognitive abilities and motor performance [4–6, 62]. These impairments impact an individual’s abilities to perform day-to-day activities and are linked to an increased risk of falls [4, 6]. Falls and related injuries lead to immobility, inactivity, loss of independence and increased dependence [62]. Early interventions aimed at maintaining activity and independence, which are specifically designed for individuals with dementia, may enable people to live well, prevent crises and reduce dependency. Exercise, strength, balance and dual-task training may have positive benefits, including improvements in gait speed and performance of activities of daily living, slowed cognitive decline and improved mood and confidence, whilst reducing the risk of falls [9–14, 29, 30].

People with MCI and mild dementia retain functional ability and independence, but are at high risk of progression and deteriorating health status. The range of neuropsychological deficits in MCI is similar to that in dementia [4, 63], and the distinction between the two is arbitrary (depending on the difficulty of daily activities considered). This provides the justification for considering the two conditions together. Pharmacological interventions are of limited efficacy in improving outcomes or slowing progression in these conditions [64]. New learning and adaptation are possible, but many interventions in dementia have proven ineffective when subject to rigorous evaluation. However, there are precedents for demonstrating effectiveness [24, 25, 27, 65]. The intervention that we describe is complex, reflecting the need to address multi-faceted problems, individual variation and real-world clinical practice. Our evaluation uses mixed research methods, to demonstrate clinical and cost-effectiveness, but also to understand how the intervention operates, what influences motivation and engagement and the necessary conditions for success and for potential future implementation.

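### Diagnosis at entry (MCI or dementia) is a foreseeable predictor of the DAD, yet it enters the primary model only if the arms happen to look imbalanced; it should be a fixed covariate

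*Protocol article*

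**What the plan says.** All references are to the protocol article.

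- **Background:** MCI "comprises cognitive impairments that do not interfere with everyday activities, but which progress to dementia at the rate of about 10% per year".
- **Sample size and justification:** "The primary outcome is the Disability Assessment for Dementia (DAD) at 12 months". The planning figure is a single one for the mixed population: "effect size 0.5 (11 points on a baseline of 70, standard deviation 22, data from [10, 13".
- **Participant inclusion/exclusion criteria:** a diagnosis of either MCI or dementia qualifies, so the diagnosis is known for every participant before randomisation.
- **Randomisation:** allocation is "stratified by site, the presence of a co-resident carer and history of previous falls". Diagnosis is not among the factors.
- **Assessment of efficacy:** "We will compare the DAD scores between the intervention and the control groups, adjusting for stratifying variables", to which the sentence adds whatever baseline characteristics prove imbalanced. For falls and the other secondary outcomes, the same section allows adjustment for variables of prognostic importance. The sentence on the DAD does not.
- **Follow-up and outcomes:** the ANCOVA takes account of baseline scores, so baseline DAD is adjusted for.
- **Discussion:** pooling is defended on the ground that the neuropsychological deficits are similar and that "the distinction between the two is arbitrary (depending on the difficulty of daily activities considered" in view.

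**The concern.** The line the Background draws between MCI and dementia runs along everyday function, and everyday function is the primary outcome. A participant with dementia is expected to start lower on the DAD and to lose more over the year than one with MCI. That can be foreseen before any data are seen.

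The stated rule treats such a variable in the wrong way. Whether to adjust for a prognostic factor should rest on its relation to the outcome, which is known in advance, and not on whether the arms happen to differ on it. A rule triggered by imbalance has two drawbacks. It makes the primary model depend on the data and on someone's judgement of what counts as imbalanced. It also gives up the precision gain in every trial where the arms look balanced, although that gain does not depend on imbalance. At stake are some precision and one avoidable analyst decision in the primary analysis.

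**Working it through.** **1. The plan's own figure.** Inputs from Sample size and justification: difference 11, SD 22, power 80%, attrition 23%. Alpha is not given in the article; two-sided 0.05 is assumed.

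- n per arm = 2(1.96 + 0.84)² / 0.5² = 63; with attrition, 63 / 0.77 = 82. The stated 184 per arm is not reproduced.
- Working back, 184 × 0.77 = 142 analysed per arm, which gives about 98.8% power for 11 points and 80% power for about 7.3 points.

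The mismatch is a separate matter. Here it matters only that the trial is larger than its stated inputs require.

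**2. Routes by which diagnosis can reach the DAD analysis.**

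| Route | Diagnosis included? |
|---|---|
| Allocation factors | No |
| Stratifying variables in the model | No, because it is not an allocation factor |
| Baseline-imbalance clause | Only if judged imbalanced |
| Prognostic-importance clause | Written for secondary outcomes, not for the DAD |
| Baseline DAD | Indirectly, as far as baseline function tracks diagnosis |

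**3. How often, and by how much, the arms might differ.** Assume 30% MCI (the share is not stated) and simple randomisation of 184 per arm. The SD of the difference in MCI share is √(2 × 0.3 × 0.7 / 184) = 0.048. The 95% range is ±1.96 × 0.048 = ±9.4 percentage points. A rule that acted only outside that range would leave diagnosis out of the model in about 95% of randomisations.

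**4. What diagnosis explains beyond baseline DAD.** Illustrative inputs, not from the protocol except the 10% and the 70:

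- Baseline DAD 93 (SD 6) in MCI and 70 (SD 22) in dementia.
- Mean fall over the year: MCI 10% × 30 = 3 points; dementia 8 to 11 points. At equal baseline DAD and a baseline slope of 1, the difference between diagnoses is γ = 5 to 8 points.
- Residual variance after baseline DAD, 22²(1 − ρ²): 363 at ρ = 0.5 and 247 at ρ = 0.7.
- Variance of the MCI indicator not explained by baseline DAD, at 30% MCI: between-diagnosis variance 0.21 × 23² = 111; within-diagnosis variance 0.3 × 36 + 0.7 × 484 = 350; so v = 0.21 × 350 / 461 = 0.159.

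Share of residual variance removed = γ²v / residual variance:

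- low: 25 × 0.159 / 363 = 1.1%
- high: 64 × 0.159 / 247 = 4.1%

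Simulations over assumed inputs gave about 3 to 7% for MCI shares of 20 to 50%, and 1 to 9% over a wider set of inputs.

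**5. What that is worth.** A cut of 1 to 9% multiplies the standard error by √0.99 = 0.995 to √0.91 = 0.954, so the interval is 0.5 to 4.6% narrower. In participants, it equals 142/0.99 − 142 = 1.4 to 142/0.91 − 142 = 14 more analysed per arm.

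**6. Size of an unadjusted chance imbalance.** At the edge of the range in step 3, the shift is about 0.094 × 5 = 0.5 to 0.094 × 8 = 0.75 DAD points, or 4 to 7% of the 11-point target.

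**The case against.** Several points on the other side stand.

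- **Diagnosis is not shut out.** The imbalance clause can bring it in, and baseline DAD carries much of its information. It would be wrong to say that diagnosis plays no part in the DAD model.
- **The estimate is unbiased.** Randomisation protects the pooled effect for the mix recruited. The analysts are to be blind to allocation, which limits steering of the covariate choice, although the choice would still follow the data.
- **The Background may be read too strongly.** It says that the cognitive impairments of MCI do not interfere with everyday activities, not that people with MCI aged 65 or over have no disability. If the boundary is as arbitrary as the Discussion holds, diagnosis may predict little and the gain lies at the bottom of the range.
- **The SAP may already settle this.** Covariates are commonly fixed there. The point is therefore not that something is missing, but that the rule the article does state is a poor one for this variable.

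A reader might go further and infer that there is little room for benefit in MCI, that the planning figures cannot describe these participants, and that power drops below 80% once MCI exceeds 33 to 46% of the sample. The documents do not support this. The effect in MCI is not given, and those shares come from assuming it to be 0 or 3 points in an unadjusted t-test. The planned analysis is an ANCOVA. At 50% MCI with no effect in MCI (5.5 points pooled, 142 per arm), power is 56% unadjusted, but 68%, 75% or 84% at a baseline correlation of 0.5, 0.6 or 0.7. With half the dementia effect in MCI, even the unadjusted test keeps 88.5%. The article also reports that feasibility data confirmed the sample size as conservative.

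**Conclusion.** The point holds as one about covariate choice. The protocol gives its own reason to expect diagnosis to predict the primary outcome, yet lets it into the primary model only through a data-dependent rule. The gain from fixing it is small: about 1 to 9% of residual variance beyond baseline DAD. That range rests on assumed MCI shares, baseline distributions and rates of decline, none of which the article gives. The case for acting rests as much on removing an analyst decision as on precision.

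A reader might also infer that pooling MCI with dementia is an error, or that the missing stratifier biases the result. Neither follows. The Discussion argues for pooling openly, and the pooled estimate is valid for the recruited population. Nor would adjusting for diagnosis alter the MCI share or how far the pooled effect depends on it. This is a low-cost improvement and not a flaw that threatens the trial.

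**What to change.** In Assessment of efficacy, and in the SAP if it does not already say so, name diagnosis at entry (MCI or dementia) as a fixed covariate in the primary DAD ANCOVA, alongside baseline DAD and the stratifying variables, whatever the observed balance.

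The cost is one degree of freedom and one line of text. The diagnosis is already known from eligibility, so no new data, staff or participants are needed. Allocation, recruitment and the pooled primary test stay as they are.

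Optionally, report the DAD difference with a 95% confidence interval within each diagnosis, labelled descriptive. The SAP may already provide for this, and its absence from the article is not a fault.

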### Aim

The aim of the study is to determine the clinical and cost-effectiveness of a therapy programme to promote activity and independence, as well as stability, amongst people with early dementia and MCI.

## Objectives and methods

The study objectives are to:
Determine whether the intervention reduces disability in ADLs; increases level of physical activity; improves balance, quality of life, mood and cognition; and decreases apathy, rate of falling, rate of hospital and care home admission, days spent in hospital and carer strainDetermine if the intervention is cost-effective, within the trial period, over the anticipated remaining lifespan of participants, using a social return on investment modelEvaluate the individual- and contextual-level mechanisms that contribute to study outcomes and evaluate the implementation of the therapy programme.

### Study design

A multi-centre, individually randomised, pragmatic, parallel-group, controlled trial will be conducted (Fig. 1). Participants will give informed consent, and will be randomised to one of two arms: the intervention arm comprising supervised therapy, or the control arm, comprising falls risk assessment and advice (Fig. 2). Mixed methods will be used to undertake process evaluation [35] and economic analyses. The Standard Protocol Items: Recommendations for Interventional Trials (SPIRIT) checklist is provided as Additional file 1.

**Fig. 1 Fig1:**
[figure not shown]
Schedule of enrolment, interventions and assessments

**Fig. 2 Fig2:**
[figure not shown]
Overview of participant-related study processes (recruitment, assessment, intervention and interviews)

### Setting

Recruitment will be from locality-based, secondary-care memory clinics, general practice registers, dementia support groups and the National Institute for Health Research (NIHR) Join Dementia Research register. Intervention sessions will be one-on-one with the participant and therapist, delivered in the participant’s home or local community.

### Recruitment

The trial will recruit 368 participants and family or carer dyads from different sites in England. Recruitment will be carried out by a study researcher, who will assess mental capacity, take consent and collect baseline data from both members of the dyad.

### Participant inclusion/exclusion criteria

Participants will be eligible to participate if they meet the following criteria: are age 65 years or older; have a diagnosis of MCI or dementia (of any subtype except dementia with Lewy bodies); have a Montreal Cognitive Assessment (MoCA) score of 13–25 (out of 30); have a family member, informal carer or friend who knows the participant well (defined as having contact with them for at least one hour per week via Internet, telephone or in person) and who is willing and able to act as an informant and be a research participant. Participants with dementia/MCI must be able to walk without human help, communicate in English, be able to see and hear, have sufficient dexterity to perform neuropsychological tests, have the mental capacity to give consent to participate and consent to do so.

Participants will be ineligible to take part if they have a diagnosis of dementia with Lewy bodies, a co-morbidity preventing participation (e.g. severe breathlessness, pain, psychosis, Parkinson’s disease or other severe neurological disease) or they expect to be unavailable over the next year (e.g. due to plans to relocate or go on a long holiday, or a life expectancy of less than a year).

Participants will discontinue the intervention if they withdraw consent or if the therapist overseeing their care decides they are no longer able to take part (e.g. due to illness or injury, progression of their disease or inability to engage despite adjustment and tailoring of the programme). Participants who withdraw will be invited to remain in the trial for collection of outcome measures if willing. Withdrawn participants who have been randomised will not be replaced, as the sample size calculations make allowance for dropout. Abrupt termination of study treatment will not affect participant safety.

For the process evaluation [35], we aim to purposively select a subsample of five participants and their carers at each of the research sites. In addition, we will invite any participants who withdraw from the study to be interviewed, to explore their reasons for withdrawal.

